| Background | One in three Medicare enrollees received their insurance beneﬁts through Medicare Advantage (MA) plan.^1^ After the passage of the Medicare Modernization Act, there has been a rapid increase in MA enrollment and use of skilled nursing facilities (SNF) for post-acute rehabilitation services compared to inpatient rehabilitation facilities. Previous studies examining utilization of rehabilitation services and the quality of care have focused on Medicare fee-for-service (FFS) patients.^2^ However, there is no information about the rehabilitation quantity, quality, and outcomes of care among MA patients staying in SNF. The Office of Inspector General reported that SNFs upcode the FFS patients into higher payment RUGs categories, leading to more hours of therapy without a substantial rise in case-mix (age and diagnoses at admission were largely unchanged from 2006 to 2008).^3^ It is unknown whether this inappropriate selection of higher paying RUG therapy group in SNFs is affecting MA patients or not and how it influences the clinical outcome in these two groups. Our group has recently published a paper about rehabilitation service utilization in patients with hip fracture among Medicare FFS beneficiaries.^2^ Jung et al. reported that there is an increase in the quantity of therapy among FFS patients with hip fracture without change in case mix at SNF admission.^2^ [name] is interested in extending this research in the MA population and comparing this with traditional FFS patients. Initially, we thought of using MDS-3 assessment completed on all Medicare- or Medicaid-certified nursing home residents irrespective of their insurance status. However, after doing a comprehensive literature review, we found that hospitals receiving a disproportionate share and educational training payments and supplements submit claims for MA beneficiaries.^4^ Therefore, we decided to use inpatient claims and HEEDIS for retrieving hospital related information. |

| **Data Sources** | **Variables** | **Link** | **Years** |
| --- | --- | --- | --- |
| Medicare Provider and Analysis Review (MedPAR) | Types of Fracture, Hospital length of stay, ICU, HCC score, hospital acquired conditions, and fracture management using ICD-9 procedure codes. | <https://www.resdac.org/cms-data/files/medpar-rif> | 2010-2015  Year 2010 was used to look back |

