| Minimum Data Set (MDS 3.0) | Admission and Discharge ADL, Pain Status, Cognition, Pain, BMI | <https://www.resdac.org/cms-data/files/mds-3.0> | 2010-2015 |
| Master Beneficiary Summary File (MBSF) | Age, Sex, Race, Marital Status, Date of death, Enrollment Status: FFS, MA, dual eligibility | <https://www.resdac.org/cms-data/files/bsf> | 2011-2015 |
| Online Survey, Certification, and Reporting System (OSCAR) | SNF Characteristics, Profit Status, Part of Chain, Staffing Pattern: Total RN/LPN FTE, PT- FTE, OT-FTE, MD-FTE | <http://www.longtermcareinfo.com/data/casper-and-oscar.php> | 2011-2015 |
| Healthcare Effectiveness Data and Information Set (HEDIS) | Capture readmission for MA patients ‘if patients will readmit to non- DSH hospitals | <https://www.resdac.org/cms-data/files/hedis-puf> | 2011-2015 |
| American Community Survey | Zip code level median household income and education. | <https://www.census.gov/programs-surveys/acs/> | 2011-2015 |
| Residential History File (RHF) | Successful Discharge to the Community | RHF create a per-person chronological history of health service utilization and location of care within a pre-specified calendar using Medicare claims and post-acute assessment data.  <https://www.ncbi.nlm.nih.gov/pmc/articles/PMC3015013/> | 2011-2015 |

**Note:** These are person-level data (i.e., MDS, MBSF, MedPAR, and HEDIS) are covered under the strict terms of a Data Use Agreement (DUA) with the Centers for Medicare and Medicaid Services (CMS). We are prohibited from making any person-level data file, no matter how de-identified, available. However, researchers interested in replicating the results of these analyses may enter into their own DUA with CMS. Please contact the Research Data Assistance Center (ResDAC) at www.resdac.org for assistance. The OSCAR/CASPER is provider-level data, and zip-code level data from the American Community Survey are available for purchase/download. **Links are provided in the table above for more information.**

**Abbreviation:** FFS- Fee-for-Service; MA- Medicare Advantage; SNF- Skilled Nursing Facilities; HCC- Hierarchical Condition Category; ICU- Intensive Care Unit; ICD-9- International Classification of Diseases, Ninth Revision, Clinical Modification (**ICD**-**9**-CM);

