| **Inclusion Criteria** | **Dataset: MedPAR Year:** January 2010 (lookback period for 2011) through June 2015  Patients admitted to hospital with hip fracture  MS-DRG codes: 533, 534, 535, and 536  Primary ICD-9-CM diagnostic codes: 82000, 82021, 82022, 82023, 82024, 82026, 82027, 82028, 82029, 82030, 82031, 82032, 8208, 82080, 82009, and 8080  Age ≥ 65 years  Patients from hospital with no information on disproportionate share  Length of stay less than 15 days  Discharged to only SNF  Admitted to SNF within 3 days of discharge from hospital  Merge with American community Survey  Exclude previous nursing home stay in past twelve months  Exclude previous hospitalization in past twelve months  **Dataset: MDS-3** - **Inclusion Criteria**  First-time SNF admissions from acute care hospitals identified on the basis of the presence of an MDS admission assessment tracking record  Include short term and long-term stay  Patients must have at least two assessments.  Patients must have first MDS assessment within 10 days of admission to SNF  Patients must have at least second or subsequent MDS (last) assessment within 10 days of discharge from SNF or any assessment.  Exclude Patients in coma  Exclude patients’ with any missing information on variables  Exclude patients’ with extreme therapy minutes and outliers  Exclude patients’ from Hawaii, Virgin Island, and Puerto Rico  Since 2008, the MedPAR file contains claims information on MA enrollees receiving care in disproportionate share hospitals (DSH) and Indirect Medical Education or Direct Medical Education adjustments. Therefore, our study cohort will be limited to patients discharged from these hospitals. |

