| **Dependent Variables** | **Function:** Functional status will be measured using seven ADL items into a 28-point scale with 0 indicating independence and 28 indicating total dependence. Change in functional status will be computed by subtracting admission from discharge scores; negative scores will be reversed to be positive to improve understanding. The more positive score the greater the improvement.  **Hospital Readmission (yes/no):** We will use all-cause readmission to the hospital within 30 days following discharge from the index hospitalization. Because MA enrollees may be readmitted to a non-DSH hospital which may not submit claims to Medicare, so we will merge the MedPAR and HEDIS files to estimate the 30-day hospital readmission for MA enrollees.  **Long-stay resident (yes/no):** SNF patient will become a long-stay nursing home resident, if they will stay in a nursing home more than 100 days.  **Successful Discharge to the community (yes/no):** Successful discharge from SNF will be defined as being discharged to the community within 100 days of SNF admission and remaining alive in the community without being institutionalized in any acute and post-acute settings for at least 30 days. We will link MDS with MedPAR and HEDIS files to estimate the Successful discharge to the community. |

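### Capture of hospital stays depends on payer, so stays missed in Medicare Advantage (MA) can lower its readmission rate and raise its successful discharge, and no planned analysis tests for this

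*Protocol*

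**What the plan says.** **Readmission.** The Dependent Variables row gives one definition for both groups: "We will use all-cause readmission to the hospital within 30 days following discharge from the index hospitalization". It then names a gap in one group, "Because MA enrollees may be readmitted to a non-DSH hospital which may not submit claims to Medicare", and the remedy for it: "so we will merge the MedPAR and HEDIS files to estimate the 30-day hospital readmission for MA enrollees". The data-sources table gives HEDIS that role alone: "Capture readmission for MA patients". No FFS source is named, so MedPAR is implied.

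**Hospital restriction.** The Inclusion Criteria row explains that MedPAR holds MA claims from disproportionate-share and medical-education hospitals. It therefore limits the cohort to patients whose index discharge was from such a hospital. It does not restrict where a later stay may occur.

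**Successful discharge.** The patient must leave for the community within 100 days of SNF admission, "remaining alive in the community without being institutionalized in any acute and post-acute settings for at least 30 days". The Dependent Variables row obtains this from a linkage of MDS, MedPAR and HEDIS, not split by group. The data-sources table instead assigns it to the Residential History File, a "per-person chronological history of health service utilization and location of care within a pre-specified calendar using Medicare claims" together with post-acute assessments. HEDIS is not mentioned there.

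**Adjustment and checks.** Original Statistical Analysis specifies inverse probability weighting on baseline characteristics and SNF fixed effects. The only sensitivity analysis named, in the Timeline, concerns 6-month and 1-year mortality.

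**The concern.** Payer is the comparison, and the completeness of event capture depends on payer. If FFS stays are fully captured and some MA stays are not, two of the four outcomes in Table 3 move in favour of MA with no true difference between the groups. A missed stay removes a readmission, and the absence of a recorded stay is part of what defines a successful discharge. That second window can run to day 100 + 30 = 130 after SNF admission, well beyond the 30-day readmission window.

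Weighting balances who is in each group. Fixed effects compare patients within a facility. Neither restores an event that was never recorded for one payer. The working hypothesis is that FFS patients do better, so an MA advantage on these outcomes would be a notable result. As planned, it could not be separated from missing data.

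**Working it through.** The protocol gives no event rate, sample size or HEDIS capture rate, so there is no stated figure to reproduce. All inputs below are assumptions. True rates are set equal in the two groups and FFS capture is taken as complete.

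**Inputs**
- r, true 30-day readmission: 10–15%
- q, share of MA hospital stays at hospitals that submit no MA claim: 10–30%
- s, share of those stays that HEDIS recovers: 50–90%
- h, hospitalised within 30 days of community discharge: 8–12%
- d, discharged to the community within 100 days: 50–70%

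**Readmission.** Under-count = r × q × (1 − s).

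| Case | Arithmetic | Points |
|---|---|---|
| Low | 0.10 × 0.10 × 0.10 | 0.10 |
| Central | 0.12 × 0.20 × 0.30 | 0.72 |
| High | 0.15 × 0.30 × 0.50 | 2.25 |

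To see what this does to an estimate, take r = 15%, q = 20% and s = 50%, so 20% × 50% = 10% of MA readmissions are missed. Observed MA readmission is 15% × 0.90 = 13.5%. That is a spurious difference of −1.5 points, with odds ratio (0.135/0.865)/(0.15/0.85) = 0.88. At two-sided 5% and 1:1 allocation, this artefact alone would be detected with 80% power at about 8,500 patients per group. With s = 90%, the missed fraction is 2% and the difference shrinks to 15% × 0.02 = 0.3 points.

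**Successful discharge.** The outcome is a proportion of all patients, so the share discharged to the community must enter. Over-count without HEDIS = d × h × q; with HEDIS = d × h × q × (1 − s).

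| Case | Without HEDIS | With HEDIS |
|---|---|---|
| Low | 0.50 × 0.08 × 0.10 = 0.4 points | × 0.10 = 0.04 points |
| High | 0.70 × 0.12 × 0.30 = 2.52 points | × 0.50 = 1.26 points |

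The with-HEDIS column applies the readmission capture range to this outcome for illustration. The protocol does not say how well HEDIS covers stays after the first 30 days.

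**Source conflict.** The Dependent Variables row uses MDS, MedPAR and HEDIS for successful discharge; the data-sources table uses the Residential History File. The first includes the MA supplement and the second, as described, does not. Which one applies decides which column is relevant.

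**The case against.** The protocol saw the readmission gap and added HEDIS because of it. With high HEDIS capture the residual bias may be a few tenths of a point. That stands: the fault is unverified residual under-capture, not failure to notice the problem.

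A reader might infer that HEDIS plays no part in successful discharge and that the Residential History File is blind to MA stays, so that any MA patient admitted to a non-submitting hospital is scored a success. The documents do not support this. The Dependent Variables row links HEDIS for this outcome. The Residential History File also uses post-acute assessments, and the Background describes "MDS-3 assessment completed on all Medicare- or Medicaid-certified nursing home residents irrespective of their insurance status", so a return to a nursing home after a missed hospital stay can be seen. The Master Beneficiary Summary File supplies date of death. The patient is wrongly counted only if HEDIS misses the stay, no assessment follows within the window, and the patient survives it.

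Nor is the net direction certain. Merging two sources could over-count some MA events. Missed prior MA stays in the 12-month exclusion could leave sicker MA patients in the cohort. Complete FFS capture in MedPAR is implied rather than stated.

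Finally, counting only claim-submitting hospitals in both groups equalises the rule, not the sensitivity, and sets aside HEDIS, the protocol's only remedy. This is a fair reason not to make it the sole headline analysis. It is no reason to omit it.

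**Conclusion.** The point holds. By the protocol's own account, MA stays can be absent from claims. The remedy applies to MA and its yield is not stated. The hospital restriction stops at the index discharge, and nothing planned tests the consequence. Under the assumed inputs, MA readmission is under-counted by 0.1 to 2.25 points. MA successful discharge is over-counted by about 0.04 to 1.3 points if HEDIS contributes as in the Dependent Variables row, and by 0.4 to 2.5 points if it does not.

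These ranges rest on complete FFS capture, equal true rates and guessed shares. They show that the bias can matter, not that it does. The conflict between the two source descriptions for successful discharge needs no assumption: it is in the text.

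**What to change.** 1. Reconcile the data-sources table with the Dependent Variables row, and state the source of each outcome separately for MA and FFS.
2. Add to Table 3, beside the planned result, an analysis with the same ascertainment rule in both groups: MDS discharge-to-hospital and re-entry records, deaths from the Master Beneficiary Summary File, and MedPAR stays counted only at claim-submitting hospitals for FFS and MA alike.
3. State in advance that an MA advantage on readmission or successful discharge will not be concluded unless it persists in that analysis.

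The cost is recoding of files already listed as data sources, provided that the MDS extract carries the discharge destination. Absolute event rates will fall in both groups, because stays at non-submitting hospitals are ignored for both. Some bias remains if MA and FFS patients use submitting hospitals to different degrees, and the report should say so.

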**Original Statistical Analysis**

There are some evidence showing cherry picking of healthier beneficiaries in MA plans and sicker patients switching from MA to FFS. There might be a level of endogeneity in the selection of MA enrollees. We anticipated that MA and FFS beneficiaries might differ with respect to demographic, clinical, and socioeconomic characteristics. To account for differences in observed demographic and clinical characteristics between FFS and MA, we will generate a propensity score that will reflect the probability of individuals to be in MA versus FFS program using observable baseline characteristics. Propensity score model will include age, gender, race, marital status, length of stay in the hospital, number of days in the intensive care unit, fracture treatment, number of comorbidities, admission cognition, body mass index, hospital-acquired complications, HCC score, dual Medicare/Medicaid status, median household income, household education and state fixed effects. After that, Inverse Probability of Treatment Weighs (IPTW) will be generated from the propensity scores to balance the differences in patient demographic and clinical characteristics.

We will compare baseline characteristics between FFS and MA using chi-square tests for categorical variables and t-tests for continuous variables then weights were applied to calculate weighted rates and mean. First, we will use linear probability model without applying IPTW to compare the difference in outcomes between MA and FFS and then we will use IPTW.

After that, we will use a linear probability model to compare outcomes between FFS and MA patients after applying IPTW and SNF fixed-effect.

**After reviewer feedback:** We added odds ratio from logistic regression models to compare the binary outcome variables for 30-day hospital readmission, becoming a long-stay resident and successful discharge to the community.

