**Recommended Tables**

**Table 1.** Characteristics of Medicare Fee-For-Service versus Medicare Advantage Patients with Hip Fracture before and after Inverse Probability of Treatment Weighting.

| **Variables** | **Unadjusted** | | **IPTW-adjusted** | |
| --- | --- | --- | --- | --- |
|  | FFS | MA | FFS | MA |
| Age |  |  |  |  |
| Female |  |  |  |  |
| Married |  |  |  |  |
| Race | | | | |
| White |  |  |  |  |
| Black |  |  |  |  |
| Hispanic |  |  |  |  |
| Others |  |  |  |  |
| Dual |  |  |  |  |
| Safety-net Hospitals % |  |  |  |  |
| Hospital Length of Stay |  |  |  |  |
| Intensive Care Length of Stay |  |  |  |  |
| HCC Score (Comorbidity Index) |  |  |  |  |
| Hospital Acquired Conditions % |  |  |  |  |
| **Fracture Treatment** | | | | |
| Open Reduction Internal Fixation |  |  |  |  |
| Close Reduction Internal Fixation |  |  |  |  |
| Internal Fixation |  |  |  |  |
| Partial Hip Replacement |  |  |  |  |
| Total Hip Replacement |  |  |  |  |
| Non-Surgical Management |  |  |  |  |
| Body Mass Index |  |  |  |  |
| Admission ADL |  |  |  |  |
| Admission Pain Status |  |  |  |  |
| **Cognition** | | | | |
| Intact |  |  |  |  |
| Mild Impairment |  |  |  |  |
| Moderate Impairment |  |  |  |  |
| Severe Impairment |  |  |  |  |
| **SNF Characteristics % and Staffing (mean ± SD)** | | | | |
| For Profit |  |  |  |  |
| Part of Chain |  |  |  |  |
| Total RN/LPN FTE |  |  |  |  |
| Total PT- FTE |  |  |  |  |
| Total OT-FTE |  |  |  |  |
| Total MD-FTE |  |  |  |  |

Cognition categories: Measured by the Cognitive Function Scale (CFS) using Cognitive Performance Scale (CPS) and Brief Interview for Mental Status (BIMS) from MDS admission assessment. Pain categories: If patient is having pain that affects sleep and functional activity in last 5 days Admission ADL score ranges from 0 - 28 (higher scores indicate more impairment). Full-time equivalent (FTE): 35 hours’/ week work in the SNF as a staff or on contract.

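### The propensity score list omits admission ADL and admission pain, so baseline function is not directly balanced between Medicare Advantage and fee-for-service patients

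*Protocol*

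**What the plan says.** The covariates are fixed in the Protocol under Original Statistical Analysis. The list opens "Propensity score model will include age, gender, race, marital status, length of stay in the hospital, number of days in the intensive care unit", continues "fracture treatment, number of comorbidities, admission cognition, body mass index, hospital-acquired complications, HCC score", and ends "dual Medicare/Medicaid status, median household income, household education and state fixed effects". The resulting weights "will be generated from the propensity scores to balance the differences in patient demographic and clinical characteristics".

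On the outcome models the same section says that "we will use a linear probability model to compare outcomes between FFS and MA patients after applying IPTW and SNF fixed-effect". It later reports, for readmission, long stay and community discharge, "We added odds ratio from logistic regression models to compare the binary outcome variables". No patient-level covariate is named in any of these models.

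Table 1 (Recommended Tables) has rows for admission ADL and admission pain status, each with unadjusted and IPTW-adjusted columns. Its footnote gives the scale: "Admission ADL score ranges from 0 - 28 (higher scores indicate more impairment". ADL change is one of four outcomes; under Dependent Variables, "Change in functional status will be computed by subtracting admission from discharge scores", with the sign then reversed so that a higher value means more improvement.

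**The concern.** The study is not randomized, and its protection against confounding by patient characteristics is the set of measured variables that enter the weights. The protocol itself warns that MA plans may attract healthier beneficiaries and that sicker ones may move to FFS. Function on arrival at the SNF is an obvious place for such selection to show. It plausibly bears on recovery of function, on the chance of becoming a long-stay resident and on the chance of going home.

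Weights balance the variables in the score. A variable left out is balanced only as far as it is correlated with those included. If MA and FFS patients still differ in admission function or pain after weighting, that difference is carried into the estimated coverage effect, and the reader cannot tell the two apart.

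**Working it through.** **1. Is the omission really there?** The three quoted parts of the list contain 6, 6 and 4 terms: 6 + 6 + 4 = 16. None is ADL or pain. The list is stated outright, so this is a choice the protocol makes and not a detail left for later.

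**2. Could availability or timing explain it?**
- The Data Sources table names the Minimum Data Set (MDS 3.0) as the source of admission ADL, pain, cognition and BMI alike.
- The Table 1 footnote takes cognition from the MDS admission assessment, and cognition is in the score.
- The Inclusion Criteria drop patients with missing information on variables, so adding the two terms should cost no patients.

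Neither availability nor timing separates the included MDS terms from the omitted ones.

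**3. Does a later step make up for it?** The planned analyses are unweighted, IPTW, and IPTW with SNF fixed effects, plus the added odds ratios. SNF fixed effects remove differences between facilities, not differences between MA and FFS patients within a facility. No step is described that uses admission ADL or pain for adjustment.

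**4. Does the change score remove baseline function?** Suppose discharge = a + b × admission within each group. Improvement is then admission − discharge = (1 − b) × admission − a. A residual MA − FFS difference D in admission ADL therefore shifts the difference in improvement by

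(1 − b) × D.

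This is zero only if b = 1. The protocol gives neither b nor D, so both are assumed here:

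| D (points) | b = 0.5 | b = 0.7 | b = 0.9 |
|---|---|---|---|
| 0.5 | 0.25 | 0.15 | 0.05 |
| 1 | 0.50 | 0.30 | 0.10 |
| 2 | 1.00 | 0.60 | 0.20 |

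With equal SDs at admission and discharge, b equals the correlation r. For r = 0.5 to 0.7 the shift is then 0.5 to 0.3 points per point of imbalance, on a 28-point scale.

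**5. Direction, if there is an imbalance.** If MA patients arrive less impaired, D is negative and their improvement is understated, which would favour the working hypothesis that FFS patients do better. For long stay and community discharge, which do not use admission ADL at all, better function would plausibly favour MA. One omission could thus push different outcomes in opposite directions.

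**6. Precision (secondary).** With equal SDs s, the variance of change is 2(1 − r)s², and the residual variance after regression on baseline is (1 − r²)s². Their ratio is (1 + r)/2: 0.75 at r = 0.5 and 0.85 at r = 0.7, a reduction of 25% and 15%. The protocol states no precision target, so this is a side benefit.

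**The case against.** - **Partial balance.** A reader might infer that functional case-mix is wholly unadjusted. The protocol does not support that. Age, cognition, HCC score, number of comorbidities, fracture treatment, hospital-acquired complications, ICU days and hospital stay may all carry information on function. The cohort also excludes patients in coma and anyone with a nursing home stay or hospitalization in the previous twelve months. Table 1 would make any remaining imbalance visible, though it would not correct it. This objection stands: the accurate term is *not directly balanced*.
- **Timing.** The first MDS assessment may fall up to 10 days after SNF admission, and pain has a five-day look-back. The study expects therapy to differ by payer, so both scores may partly reflect early payer-dependent care, and adjusting for them could remove some of the effect under study. This is a real but small cost. It does not defeat the change, because cognition from the same assessment is already in the score. ADL and pain are nearer to what therapy targets, which is a reason to show both analyses.
- **Change score versus baseline adjustment.** In non-randomized groups the two methods rest on different assumptions and can legitimately disagree, and measurement error at baseline leaves the adjustment incomplete. So (1 − b) × D is a bias only if the baseline-adjusted model is right, and it concerns ADL change alone. That stands.
- **Outcome models.** A reader might infer that the protocol rules out covariates in them. It does not; it names none. The firm part of the point is the explicit propensity list.

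**Conclusion.** The point holds in a limited form and should be fixed. Weights meant to balance clinical characteristics do not target admission ADL or admission pain, two characteristics that the protocol's own Table 1 presents as baseline and that are held in the same data source as terms already used. This leaves avoidable confounding possible in all the MA–FFS comparisons, and the raw change score does not remove it for ADL if the admission-to-discharge slope is below 1.

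The size is illustrative only: 0.3 to 0.5 points of ADL change per point of residual imbalance for r = 0.7 to 0.5, and 0.05 to 1.0 points over the wider grid above. No figure of this kind can be given for pain or for the binary outcomes. It would be tempting to conclude that the results are biased by a known amount or in a known direction. The protocol does not support this: it reports no imbalance, slope or correlation, and its remark on healthier MA enrollees concerns enrollment, not function after a fracture.

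**What to change.** 1. Add admission ADL and admission pain status to the propensity score model.
2. Include admission ADL as a covariate in the weighted ADL-change regression, with and without SNF fixed effects.
3. Report post-weighting standardized differences for both variables beside the Table 1 means and percentages.
4. Report the results with and without the added terms as a sensitivity analysis, and say that the first assessment may come up to 10 days after SNF admission.

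The cost is small: two more terms in one model and one in another, with data already held and complete under the eligibility rules, and a rerun of the weights and the weighted analyses. The one drawback is the possible adjustment for early payer-dependent care, which item 4 brings into view. If the omission was deliberate, the protocol should give the reason and still report item 3.

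### Fracture type is listed as a MedPAR variable but is absent from the propensity score, the outcome models and Table 1, so any remaining payer difference in injury mix would be neither adjusted for nor visible

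*Protocol*

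**What the plan says.** The MedPAR row of the Data Sources table names "Types of Fracture, Hospital length of stay, ICU, HCC score, hospital acquired conditions, and fracture management using ICD-9 procedure codes". Type of fracture and management of fracture are thus two separate items from the same source.

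The Inclusion Criteria define the cohort by "MS-DRG codes: 533, 534, 535, and 536" and by "Primary ICD-9-CM diagnostic codes: 82000, 82021, 82022, 82023, 82024, 82026, 82027, 82028, 82029, 82030, 82031, 82032, 8208, 82080, 82009, and 8080".

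Original Statistical Analysis says that the propensity score is meant to account for observed demographic and clinical differences between FFS and MA. Its list opens with age, gender, race and marital status, continues with "length of stay in the hospital, number of days in the intensive care unit, fracture treatment, number of comorbidities", and closes with "admission cognition, body mass index, hospital-acquired complications, HCC score, dual Medicare/Medicaid status, median household income, household education and state fixed effects". The outcome models are then described as linear probability models, first unweighted, then with IPTW, then with IPTW and SNF fixed effects. Logistic models were added later for the binary outcomes.

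In Recommended Tables, the Table 1 shell has a block headed "Fracture Treatment" with six categories. It has no row for fracture type or diagnosis code.

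**The concern.** The comparison of payers is not randomised, and the protocol itself expects MA and FFS beneficiaries to differ clinically. The weights are the main defence, and Table 1 is where a reader checks whether they worked. The injury that brought the patient into the cohort is observed, clinical and fixed before any care is given, so it fits the stated purpose of the propensity score. It is left out without a reason, while hospital length of stay, ICU days and hospital-acquired complications, which arise during care, are included.

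If fracture type is related to recovery and its mix differs by payer, the estimates for SNF stay, therapy minutes, ADL change, readmission, long stay and discharge to the community would all carry part of that difference. The first condition is ordinary clinical reasoning and the second is a possibility; the protocol gives figures for neither.

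**Working it through.** The protocol states no figure on this point, so there is none to reproduce. The check sets its parts side by side.

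| Place in protocol | Fracture type | Fracture treatment |
| --- | --- | --- |
| Data Sources, MedPAR row | listed | listed separately |
| Inclusion Criteria | 16 primary diagnosis codes pooled | not used |
| Propensity list (16 terms) | absent | 1 term |
| Outcome models | absent | through the weights only |
| Table 1 | 0 rows | 6 rows |

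**How mixed the cohort is by code.** Grouping the sixteen codes by their leading digits gives 8200x: 2; 8202x: 8; 8203x: 3; 8208 and 8208x: 2; 8080: 1. The sum is 2 + 8 + 3 + 2 + 1 = 16. This shows that several code groups are pooled. It does not show that they differ in prognosis.

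**Whether a later step recovers the variable.** The only sensitivity analysis named, in the Timeline, concerns mortality at 6 months and 1 year. No stratification by fracture type is planned. SNF fixed effects remove differences in injury mix between facilities, but not differences between payers within a facility.

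**What would remain.** For each fracture group, let d be the FFS minus MA difference in that group's weighted share, and g the difference in outcome between that group and a reference group, given the other covariates. The residual bias in a mean or risk difference is approximately the sum of d × g over the groups.

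- If weighting on treatment and the other fifteen terms happens to balance fracture type, every d is 0 and so is the bias.
- If some d are not 0, the bias depends on d and g, and the protocol supplies neither.

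Purely to show how the formula scales, with assumed inputs for one group: d of 2 to 10 percentage points and g of 5 to 15 points of risk give 0.02 × 0.05 = 0.001 to 0.10 × 0.15 = 0.015, that is 0.1 to 1.5 percentage points. None of these inputs comes from the document, so the range is not an estimate and the conclusion does not rest on it.

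The IPTW-adjusted columns of Table 1 would show d directly if fracture type had rows there. As laid out, they cannot.

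**The case against.** The best defence is that fracture type is already covered indirectly. Treatment has six categories, including partial replacement, total replacement and non-surgical management, and the model also holds age, gender, cognition, body mass index, comorbidities, HCC score, hospital stay and more. Only imbalance independent of all of these would be left. That is right, and it may make the remainder small. But nothing in the protocol maps the sixteen codes to the six treatments, and balance on treatment does not guarantee balance on injury within treatment.

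It can also be said that the Data Sources table is not a covariate plan, that diagnosis codes have a stated use in selecting the cohort, that the propensity list need not be exhaustive, and that the tables are only recommended. So the protocol does not contradict itself. Still, no part of it says that fracture type is to be added.

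Three stronger readings are tempting and are not supported:

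- **That the payer estimates are biased, or biased by a given amount.** The document gives no evidence that injury mix differs by payer. Its stated selection worry is healthier people entering MA and sicker people moving to FFS.
- **That treatment is a poor covariate because it is chosen after payer status is set.** The fracture also follows enrolment, so this does not separate the two. What does is that fracture type is fixed before care, whereas treatment is a decision within it.
- **That code 8080 calls for a sensitivity analysis on this ground.** Whether it belongs in the cohort is a question of case definition, separate from the choice of covariates.

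**Conclusion.** The point holds as a gap in the adjustment set and the balance table. A baseline variable that the protocol lists, and that serves the stated aim of the propensity score, is neither weighted on nor displayed. What follows is a risk of residual confounding of unknown size and direction, limited to whatever treatment and the other covariates do not capture. It becomes an actual bias only if two conditions both hold, given those covariates: fracture mix differs by payer, and fracture type is related to the outcome. The document establishes neither. The point is therefore a worthwhile low-cost improvement and no reason to reject the planned analysis.

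**What to change.** In Original Statistical Analysis, add fracture type to the propensity model as a categorical term built from the primary diagnosis code. The groups 8200x, 8202x, 8203x, 8208/8208x and 8080 are a natural starting point, with sparse groups collapsed by a rule based on counts and set without reference to outcomes. Five groups add at most 5 − 1 = 4 parameters. In Table 1, add the same groups as rows in both the unadjusted and the IPTW-adjusted columns. If the investigators prefer to leave fracture type out of the weights, the protocol should give the reason, and the Table 1 rows should be added all the same.

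The cost is small but not nil. No new source is needed, since the variable is already among those listed from MedPAR. However, the weights must be refitted and Tables 1 to 3 rerun, and the Timeline shows the weighted analysis presented in May 2017. Small code groups could make the weights slightly more variable, which is why they should be collapsed.
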